## Abstract

**Introduction:**

Girls’ and women’s health as well as social and economic wellbeing are often negatively impacted by early childbearing. In many parts of Africa, adolescent girls who get pregnant often drop out of school, resulting in widening gender inequalities in schooling and economic participation. Few interventions have focused on education and economic empowerment of adolescent mothers in the region. We aim to conduct a pilot randomized controlled trial in Blantyre (Malawi) and Ouagadougou (Burkina Faso) to examine the acceptability and feasibility of three interventions in improving educational and health outcomes among adolescent mothers and to estimate the effect and cost-effectiveness of the three interventions in facilitating (re)entry into school or vocational training. We will also test the effect of the interventions on their sexual and reproductive health (SRH) and mental health.

**Interventions:**

The three interventions we will assess are: a cash transfer conditioned on (re)enrolment into school or vocational training, subsidized childcare, and life skills training offered through adolescent mothers’ clubs. The life skills training will cover nurturing childcare, SRH, mental health, and financial literacy. Community health workers will facilitate the clubs. Each intervention will be implemented for 12 months.

**Methods:**

We will conduct a baseline survey among adolescent mothers aged 10–19 years (N = 270, per site) enrolled following a household listing in select enumeration areas in each site. Adolescent mothers will be interviewed using a structured survey adapted from a previous survey on the lived experiences of pregnant and parenting adolescents in the two sites. Following the baseline survey, adolescent mothers will be individually randomly assigned to one of three study arms: arm one (adolescent mothers’ clubs only); arm two (adolescent mothers’ clubs + subsidized childcare), and arm three (adolescent mothers’ clubs + subsidized childcare + cash transfer). At endline, we will re-administer the structured survey and assess the average treatment effect across the three groups following intent-to-treat (ITT) analysis, comparing school or vocational training attendance during the intervention period. We will also compare baseline and endline measures of SRH and mental health outcomes. Between the baseline and endline survey, we will conduct a process evaluation to examine the acceptability and feasibility of the interventions and to track the implementation of the interventions.

**Discussion:**

Our research will generate evidence that provides insights on interventions that can enable adolescent mothers to continue their education, as well as improve their SRH and mental health. We aim to maximize the translation of the evidence into policy and action through sustained engagement from inception with key stakeholders and decision makers and strategic communication of research findings.

*Trial registration number* AEARCTR-0009115, May 15, 2022.

## Background

Early childbearing in sub-Saharan Africa is associated with negative impacts on girls’ physical and mental health, and socio-economic wellbeing including school dropout [1–3]. Research has shown that many adolescent mothers would like to return to school but lack the needed support to pursue their educational goals [2, 4]. While some countries in the region have policies that ensure that pregnant girls are supported to continue with learning during pregnancy and return to school after they have delivered, their implementation is lacking. Instead, girls who get pregnant while at school face stigma, abuse, violence, or rejection and often receive little or no support from their families, school administrators and the community [4]. These issues present serious challenges for pregnant girls and adolescent mothers hoping to continue their education [5]. Without developing effective approaches to ensure the re-entry into school for the millions of girls dropping out of schools each year because of unintended pregnancy, sub-Saharan African countries will not achieve gender equality in schooling.

Adolescent mothers are also at risk for rapid repeat pregnancies (defined as a second pregnancy within 24 months of the first pregnancy), if not provided with adequate care and support [6]. Such closely spaced births further exacerbate their risk of adverse pregnancy outcomes and negative consequences [7, 8]. Research has shown that adolescent mothers in sub-Saharan Africa have the highest prevalence of short birth spacing [9]. In a recent analysis, the overall prevalence of contraceptive use among adolescents in the region was 21%, ranging from 70% in South Africa to only 5% in Chad [10]. In one study conducted in Kenya, women who gave birth between the ages of 15 and 24 years were more likely to discontinue postpartum contraceptive use than women who gave birth at older ages [11]. Investing in their postpartum contraceptive use has several health and socioeconomic benefits, including allowing adolescent mothers to pursue education and vocational skills development and protect their physical and mental health. Such investment would have twin benefits including preventing repeat pregnancy and HIV and other sexually transmitted infections (STIs).

Despite the negative consequences of adolescent childbearing for girls’ education, health and social wellbeing, and gender equality, few interventions have focused on education and economic empowerment of parenting adolescents in Africa. Improving health and social outcomes for pregnant and parenting adolescents will require interventions that challenge the gendered social norms and hierarchies that perpetually limit parenting girls’ education, financial opportunities and economic security. Promising multilevel interventions for girls’ empowerment like the Adolescent Girls Initiative—Kenya (AGI-K), have been shown to lead to violence reduction, primary school completion, increased sexual and reproductive health (SRH) knowledge, financial literacy and savings, and positive gender norms [12]. However, it is unclear if, at all, such interventions can increase adolescent mothers’ re-entry into school and vocational training, and improve SRH and mental health outcomes among them.

To address this gap, we aim to implement a pilot randomized controlled trial (RCT) in Burkina Faso and Malawi to address the social exclusion of adolescent mothers and foster their re-entry into school or vocational training while enhancing their life skills. We chose Burkina Faso and Malawi because both countries face a huge burden of adolescent childbearing but have contrasting policy contexts on school re-entry. While girls’ education remains a key priority of decision-makers in Burkina Faso [13], there is no clear policy or guideline for supporting pregnant girls in schools. In Malawi, the Readmission Policy for Primary and Secondary Schools allows school-aged mothers to resume school after giving birth, reversing a previous policy that banned them from re-enrolling [14, 15]. Under the current policy, after delivery, adolescent mothers can request for readmission from both the Ministry of Education and the school [14]. However, the extent to which this policy is effective in facilitating school re-entry of parenting adolescents is unknown.

The three interventions we will assess are: (1) a cash transfer conditioned on (re)enrolment into school or vocational training and continued attendance; (2) subsidized child care; and (3) adolescent mothers’ clubs where adolescent mothers will receive life skills training covering nurturing childcare, SRH, and financial literacy. The choice of these interventions is informed by previous research highlighting financial constraints and lack of childcare as major barriers to school re-entry for parenting adolescents [3, 4]. These interventions also build on existing initiatives that provide a platform for scaling up should our research demonstrate their effectiveness. For example, the Government of Malawi runs the Social Cash Transfer Programme (SCTP), which provides ultra-poor and labor-constrained households an unconditional monthly transfer of about 7000 Malawian Kwacha (~ US$ 8.7) [16]. Currently, adolescent mothers are not targeted in the SCTP. The SCTP provides a framework for implementing cash transfers to parenting adolescents.

The specific objectives are to: (1) test the feasibility and acceptability of the interventions in the study contexts; (2) determine which combination(s) of interventions (cash transfer, subsidized child care, and adolescent mothers clubs) lead to the greatest increase in adolescent mothers’ re-entry into school or vocational training (primary outcome); (3) assess the effects of different combinations of the interventions on SRH and mental health outcomes among adolescent mothers (secondary outcomes); and (4) assess the cost-effectiveness of these interventions in increasing adolescent mothers’ re-entry into school or vocational training.

We hypothesize that these interventions will enhance adolescent mothers’ social, economic, health and education assets thereby allowing them to (re)enroll into school or vocational training. We also hypothesize that building these assets will lead to improved SRH and mental health outcomes for these mothers. Additionally, we hypothesize that combining the conditional cash transfer, subsidized child care and adolescent mothers’ club interventions is more effective in increasing re-entry into school and vocational training than adolescent mothers’ clubs only or combined adolescent mothers’ clubs and subsidized child care interventions.

## Theoretical framework

Our research is guided by the ecological framework, which underscores the importance of an enabling environment for adolescents’ health and development. Barriers that hinder pregnant and parenting adolescent girls’ education and economic empowerment operate at multiple levels, including at individual, household and community levels. Interventions that address these multiple levels of barriers are more likely to be effective than those that focus on a single level [17].

At the individual level, it is important to focus on interventions that empower parenting adolescents by building their social, economic, health and education assets. In this respect, our proposed interventions seek to empower adolescent mothers by providing them with cash transfers conditioned on re (enrolment) into school or vocational training and continued attendance. Adolescent mothers will also receive life skills training on SRH, nurturing care for children, and financial literacy. The training will be provided through adolescent mothers’ clubs, which are modeled on the Population Council’s Safe Spaces groups [18], where adolescent mothers will meet in groups under the guidance of a community health worker. The community health workers (CHWs) will also support adolescent mothers in accessing contraceptives and other SRH services through referrals to adolescent-friendly SRH providers. Further, the clubs will help in creating social solidarity and serve as a social support network to empower adolescent mothers to collectively address the issues they face in their daily lives including social stigma associated with adolescent pregnancy. In light of research showing that lack of child care is a significant barrier to school re-entry for parenting adolescents, our intervention will also include vouchers for subsidized child care in registered childcare facilities/crèches.

Given the potential for contamination, we will not test a community wide intervention. However, we will conduct community dialogues aimed at engaging a variety of community members including community and religious leaders, health workers, social workers, teachers, and parents. The goal of these community dialogues will be to identify the root causes of adolescent pregnancies, including gender norms; to discuss possible ways to support parenting adolescents, including addressing stigma against pregnant and parenting adolescents; and to develop a sense of ownership in collectively supporting these adolescents.

While our interventions do not address societal level factors, our research uptake activities will focus on promoting laws (including community by laws) and policies that support parenting adolescents to realize their rights, including their rights to education and comprehensive SRH interventions. Figure 1 summarizes our theory of change.

**Fig. 1 Fig1:**
[figure not shown]
PROMOTE project theory of change

## Methods

### Study design

We will conduct a pilot RCT designed to estimate the effect of a conditional cash transfer and subsidized child care on adolescent mothers’ re-entry into school or vocation training. We also seek to examine the effects of the interventions on SRH outcomes and mental health as secondary outcomes, and to determine the most cost-effective interventions to increase adolescent mothers’ re-entry into school or vocational training. We will randomly assign adolescent mothers to one of three study arms. Adolescent mothers in all the arms will receive life skills training through adolescent mothers’ clubs. Adolescent mothers in arm two will also receive subsidized child care, while those in arm three will receive all three interventions. Comparing arm one (mothers’ clubs only) and arm two (mothers’ clubs + subsidized child care) will allow us to test the additional benefit of the subsidized child care. Comparing arms two and three (mothers’ clubs + subsidized child care + cash transfer) will also allow us to test the additional benefit of the cash transfer. Comparing arms one and three will allow us to test the combined benefit of the subsidized child care and cash transfers. The RCT design is summarized in Fig. 2.

**Fig. 2 Fig2:**
[figure not shown]
Pilot randomized controlled trial design for the PROMOTE Project

### Study sites

The study will be conducted in urban settings in Ouagadougou (Burkina Faso) and Blantyre District (Malawi). We selected these settings given previous research showing low school enrollment among pregnant and parenting adolescents. In a survey conducted in Ouagadougou, Burkina Faso, 82% of pregnant and parenting adolescents were out of school, with 23% reporting that they dropped out of school because of pregnancy [19]. Among those out of school in Burkina Faso, 39% wanted to return to school, while 79% wanted to have an income generating activity. Girls reported the lack of childcare support, stigma, and inadequate support as some of the barriers to school re-entry.

A similar survey conducted in Blantyre District in Malawi found that poverty, sexual violence, inequitable gender norms, and lack of access to accurate contraceptive information and services make girls vulnerable to early and unintended pregnancy [4]. Most girls get pregnant outside of marriage and consequently face social exclusion from their peers, parents and communities. While most rely on their parents to provide for them and their babies, some depend on their partners. However, most face dire financial situations, sometimes lacking food and other basic needs. Approximately 94% of adolescents surveyed were out of school, and about half of them dropped out because of pregnancy. However, 76% of them wanted to return to school if provided with financial and childcare support, while 93% wanted to learn vocational skills [4].

### Interventions

Each intervention will be implemented for 12 months. Below, we describe each intervention:

#### Adolescent mothers’ clubs

The adolescent mothers’ clubs will be held every two weeks for 12 months in a variety of locations in the community considered by adolescent mothers to be safe and appropriate for them to meet. During the club meetings, adolescent mothers will receive life skills training facilitated by trained CHWs. The club will create a safe space where adolescent mothers can interact to discuss their common problems, learn about child care, mental health, HIV, SRH (including harmful gender norms that raise the risk of experiencing and tolerating sexual and gender-based violence), conflict resolution, hygiene, and financial literacy (e.g., making a savings plan, spending priorities, and where to save).

Because the burden of poor mental health is significant among adolescent mothers [20], the club will also offer a safe space where these adolescent mothers can receive psychosocial support from CHWs and peers. The collectivism the club creates also has the potential for strengthening their self-esteem, a resource they need to address the stigma associated with adolescent childbearing. Given their role as a bridge between the community and the health sector, we also expect that the CHWs will also facilitate adolescent mothers’ access to SRH and child health services. CHWs will also refer any adolescent mothers needing additional psychosocial support to child protection workers, who work at community level.

The CHWs will follow a structured curriculum that has been adapted from the Population Council’s AGI-K Safe Spaces curriculum. [21]; the Mphatlalatsane (Early Morning Star) Health and Nutrition Programme Manual [22]; the Maternal and Child Health Handbook [23] and the Parenting for Lifelong Health Programme for Young Children (Facilitator manual) [24]. The CHWs will undergo a 5-day training workshop on the curriculum. The workshop will be facilitated by the research team and will adopt a participatory approach that will also serve to demonstrate the participatory methods to be used by CHWs during the adolescent mothers’ clubs.

Each adolescent mothers’ club will include about 15–25 adolescent mothers living within the same locality. The sessions will be approximately 2 h long. CHWs will monitor and record attendance and will follow up adolescent mothers who miss sessions.

#### Subsidized child care

Vouchers have been effectively used for childcare in Kenya [25]. Adolescent mothers in arms two and three will receive vouchers for subsidized childcare in selected childcare centers in the two study sites. Adolescent mothers who receive the vouchers will be entitled to 12 months of subsidized childcare. In Malawi, we will work with community-based childcare centers (CBCCs), which are managed by community members and overseen by the Ministry of Gender, Community Development and Social Welfare. These centers depend on contributions from the community and parents are expected to contribute a nominal amount towards the running of these centers [26]. In Burkina Faso, we will work with a mix of public and private preschools as well as community-based childcare centers. In the inception period, we will map out childcare centers and conduct brief interviews with the childcare center managers/teachers to understand the level of financial support needed. The information obtained will help us identify specific centers where adolescent mothers can send their children, as well as help us establish a reasonable voucher amount. Adolescent mothers who are eligible to receive vouchers will receive 12 vouchers. They will hand over a voucher to the respective childcare center at the beginning of every month. In each study setting, field staff will collect the vouchers from each childcare center to monitor the intervention, as well as to determine the exact amount to be transferred to each childcare center.

#### Conditional cash transfers

The cash transfer will be conditioned on (re)enrolment in primary or secondary school (junior and senior high school in Burkina Faso) or vocational training programs. A Cochrane systematic review [27] showed that cash transfer programs that are conditional and that incorporate systems to monitor compliance and that penalize non-compliance have greater effects on enrolment. Transfers will be made for every term during the intervention period that the girl is enrolled and remains enrolled. During the intervention period, field staff will visit schools at regular intervals to confirm adolescent mothers’ continued enrolment.

Adolescent mothers in arm three will receive a cash transfer every three months. Each transfer will be approximately US$ 30 (US$ 10 per month) and will be transferred through mobile money platforms, which are common in Burkina Faso and Malawi. Cash transfers to mobile phone-based money transfer services have been successfully used in similar settings [28].

### Outcomes

#### Primary outcome

The primary outcome of this study is (re)entry or (re)enrolment in school or vocational training. At baseline, all participants will respond to a question on current school and vocational training enrolment and their intention to return to school or vocational training. At endline, participants will be asked whether they have attended school or vocation training at any time after the baseline. The primary outcome will be a binary variable coded 1 “Yes” or 0 “No” indicating whether or not the participant was enrolled in school or vocation training during the 12-month long intervention period.

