### Eligibility criteria

Eligible participants will comprise adolescent mothers aged 10–19 years who:Have at least one biological child aged 1–3 years.Can speak and understand the main language used in the mothers’ clubs in the study context.Have been resident in the study site for at least 1 year.Consent/assent to being in the study (and, for minors, whose parents/guardians provide consent).

Adolescent mothers who are living with disability will be eligible to participate as long as they meet the eligibility criteria.

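### Mothers already in school or training at baseline are eligible and score as (re)entry successes, which dilutes the primary contrast and mislabels what is reported

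*Protocol article*

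**What the plan says.** Objective (2) in the Background concerns re-entry and labels it the primary outcome. The Primary outcome section agrees in name: "The primary outcome of this study is (re)entry or (re)enrolment in school or vocational training". The coding in the same section is wider. At endline "participants will be asked whether they have attended school or vocation training at any time after the baseline", and the variable is binary, "indicating whether or not the participant was enrolled in school or vocation training during the 12-month long intervention period". Neither sentence refers to the mother's status at baseline.

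That status is known: at baseline "all participants will respond to a question on current school and vocational training enrolment". It is not used to define the outcome, does not appear in the Covariates list, and is not an entry condition. The Eligibility criteria cover age, language and consent, plus "Have at least one biological child aged 1–3 years" and "Have been resident in the study site for at least 1 year". The Exclusion criteria are current pregnancy and inability to take part in the clubs.

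Data processing and analysis calls for an unadjusted intention-to-treat primary analysis. It speaks of comparing enrolment at the two surveys but does not set aside or recode mothers enrolled at the first. On how many there may be, Study sites reports that in Ouagadougou "82% of pregnant and parenting adolescents were out of school", and gives about 94% for Blantyre.

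**The concern.** A mother in school or training at baseline cannot re-enter, yet she scores 1 after any attendance during the following year. The coding does not measure retention for her either, because one early attendance followed by dropout also scores 1. Such mothers add near-certain successes to every arm, so the difference between arms shrinks.

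Three results are affected. The primary comparison loses power. The effect estimate, which the sample size section wants for planning a larger trial, is attenuated. The re-entry percentages reported for each arm are too high, so an average cost per (re)enrolled mother calculated on coded successes would look too low.

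**Working it through.** **The plan's own figure.** Inputs from Sample size and sample selection: 94% v 79% not in school, two-sided 10%, 80% power, design effect 1.1, 15% loss, 90 per arm. The printed formula gives 63.1, so 64 per arm. Inflated, 64 × 1.1 / 0.85 = 82.8, so 83 per arm. The stated 90 exceeds this, so it is not a shortfall. The effective size at 90 per arm is 90 × 0.85 / 1.1 = 69.5, at which 94% v 79% has about 83% power.

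**Dilution.** Let f be the share enrolled at baseline, all scoring 1, and r the re-entry rate among the rest.

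- Coded rate = f + (1 − f) × r.
- Coded difference = (1 − f) × difference in r.
- Blantyre, f = 6%: 0.94 × 15 = 14.1 points.
- Ouagadougou, f = 18%: 0.82 × 15 = 12.3 points.

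**Power.** The documents do not give arm-one re-entry among out-of-school mothers, so I vary it from 0% to 16%; the top is the upper end of the Kenyan range cited in the sample size section. The effect among out-of-school mothers is fixed at 15 points. The test is a two-proportion comparison with pooled variance at two-sided 10%. As coded, effective n is 69.5 per arm. Restricted to mothers not enrolled at baseline, it falls to 69.5 × 0.94 = 65.4 in Blantyre and 69.5 × 0.82 = 57.0 in Ouagadougou.

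| Site | Arm-one re-entry | Coded rates compared | Power as coded | Power restricted |
|---|---|---|---|---|
| Blantyre | 0% | 6.0% v 20.1% | 80% | 95% |
| Blantyre | 6% | 11.6% v 25.7% | 69% | 81% |
| Blantyre | 10% | 15.4% v 29.5% | 64% | 73% |
| Blantyre | 16% | 21.0% v 35.1% | 58% | 65% |
| Ouagadougou | 0% | 18.0% v 30.3% | 52% | 93% |
| Ouagadougou | 6% | 22.9% v 35.2% | 48% | 76% |
| Ouagadougou | 10% | 26.2% v 38.5% | 46% | 68% |
| Ouagadougou | 16% | 31.1% v 43.4% | 44% | 60% |

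The restricted analysis has more power in every row despite its smaller n.

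**Mislabelling.** The share of arm-one successes already enrolled at baseline is f divided by the coded arm-one rate. In Ouagadougou it runs from 100% (r = 0) to 0.18 / 0.3112 = 58% (r = 16%). In Blantyre it runs from 100% to 0.06 / 0.2104 = 29%.

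**The other reading of the planning figures.** If 94% v 79% describes the whole sample, girls in school included, the 6% is already counted and Blantyre keeps its 83%. This reading leaves no room for re-entry in arm one and needs 15 / 0.94 = 16.0 points among out-of-school mothers. The same 15 points overall from Ouagadougou's 82% out of school (18% v 33% enrolled) has about 65% power at 90 per arm, and would need 104 per arm before inflation and 135 after.

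**The case against.** The strongest reply is that the planning proportions already cover girls in school. Read that way, Blantyre has no shortfall against its plan. This stands: a reader might infer from the table that the coding leaves Blantyre below its planned 80%, but that follows only if the 15 points are taken as an effect among out-of-school mothers. The reply does not cover Ouagadougou, where the same 270 per site is used with a different share out of school.

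Second, the 6% and 18% come from surveys of pregnant and parenting adolescents and describe schooling only. The trial excludes pregnant girls and requires a child aged 1–3 years. The share in the trial population is not given and could be higher or lower; any mothers already in vocational training would add to it.

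Third, a reader might conclude that the outcome does not measure re-entry at all, or that the arms are compared unfairly. Neither is supported. On the survey figures most participants are out of school, so the outcome still depends largely on re-entry, and enrolled mothers are balanced across arms in expectation.

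Fourth, in an incremental cost-effectiveness ratio the continuing students cancel in expectation. Only an average cost per (re)enrolled mother is distorted.

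Finally, the analysis section mentions baseline enrolment and adjustment for baseline differences, and an unseen analysis plan may say more. But the article does fix the outcome coding, that coding does not match the objective, and the primary analysis is unadjusted.

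**Conclusion.** The point holds as dilution and mislabelling. The stated coding counts continuing enrolment as (re)entry, and nothing in the article's eligibility, covariates or primary analysis corrects for it. The contrast is multiplied by about 0.94 in Blantyre and 0.82 in Ouagadougou. Compared with restricting to mothers not enrolled at baseline, the coded outcome gives up about 7 to 15 points of power in Blantyre and 16 to 41 in Ouagadougou.

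These sizes assume that the survey shares roughly apply, that every mother enrolled at baseline scores 1 in every arm, that the effect among the others is 15 points, and that arm-one re-entry lies between 0% and 16%. The direction does not depend on the exact figures; the size does. The consequence is clearly material in Ouagadougou and smaller in Blantyre.

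**What to change.** - Define the primary analysis set as all randomised mothers who reported at baseline that they were in neither school nor vocational training. Status is recorded before allocation, so the comparison remains randomised and intention-to-treat within that set.
- Define success as a new enrolment in school or vocational training within 12 months of randomisation.
- Report mothers enrolled at baseline separately, with a retention measure that one attendance alone cannot satisfy.
- Bring the Primary outcome and Data processing and analysis sections into line with this, and base the average cost per (re)enrolled mother on new enrolments.

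The cost is wording plus a smaller primary set. On the survey figures about 0.06 × 90 = 5 mothers per arm leave it in Blantyre and 0.18 × 90 = 16 in Ouagadougou, more if some are already in vocational training. No new baseline data are needed. Changing the eligibility criteria is optional and not required.
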